## Description of study evaluations/measurements/assessments

## Primary Endpoint

The rate of surgical site infection till 30 days after surgery (90 days if implant) using CDC definition of SSI in pre-intervention versus post-intervention phase for clean, clean-contaminated and contaminated surgeries (Annexure-II, III).

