## Statistical analysis plan

The data collected in the antimicrobial audit form will be analysed after entry into the excel form. The antimicrobial consumption analysis will be done using Microsoft excel. The descriptive data analysis will be done using Statistical package for the social sciences (SPSS) Version 23. The rate of surgical site infection till 30 days after surgery (90 days if implant) will be expressed as events per person-time, separately for clean, clean-contaminated, contaminated surgeries. All secondary endpoints will be expressed as mean, standard deviation (if the variable is quantitative) or as frequency, percentage (if the variable is categorical). The rates of primary outcome and secondary outcomes measured at the study centres in post-intervention will be compared with the pre-intervention/baseline data to assess the impact of the intervention. Chi-square test, independent sample t test or Mann-Whitney U test will be used for the statistical comparisons.

Plots and pivot tables will be generated using statistical software or excel as appropriate. The analysis will be conducted separately for clean, clean-contaminated and for contaminated surgeries. A sub-group analysis will also be conducted as per the level of fidelity.

Kaplan Meier curves will be plotted to demonstrate the incidence rates of surgical site infections. The difference in the rate of surgical site infections between the nature of surgeries (clean, clean-contaminated, contaminated surgeries), or any other exposure categories will be statistically tested using the log-rank test. A Cox proportional hazard model will be constructed to identify the predictors of surgical site infections.

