## Sample Size and Power

The three strata based on the type of the surgery (clean, clean-contaminated and contaminated) will be separately powered, based on different baseline SSI rates extracted from Indian study showing prevalence of SSIs in general surgery patients.^7,8^ The sample sizes were based on 90% power, a 5% two-sided significance level and 15% loss to follow up or death before reaching the primary endpoint at 30-days. For the clean surgeries, anticipating the baseline average SSI rate of 8%, a 3% absolute reduction in SSI to 5% will be taken as clinically significant and would require 3260 patients in total (1630 patients in pre-intervention and intervention each). For the clean-contaminated surgeries, anticipating the baseline average SSI rate of 12%, a 4% absolute reduction in SSI to 8% will be taken as clinically significant (i.e relative risk of 0.67) and would require 2700 patients in total (1350 in pre-intervention and intervention each). For the contaminated surgeries, anticipating higher baseline SSI rate of 30%, a 10% absolute reduction in SSI to 20% will be taken as clinically significant and would require 900 patients in total (450 in pre-intervention and intervention each).

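### Kaplan-Meier curves are named to show SSI incidence although deaths before SSI are expected; cumulative incidence with death as a competing event should replace them

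*Protocol*

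**What the plan says.** Section 3.9 (Statistical analysis plan) and the matching synopsis entry assign several tools to the SSI outcome:

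- Display: "Kaplan Meier curves will be plotted to demonstrate the incidence rates of surgical site infections".
- Comparison of curves: differences between wound classes "or any other exposure categories will be statistically tested using the log-rank test". A Cox model for predictors of SSI follows.
- Expression of the primary outcome: it "will be expressed as events per person-time, separately for clean, clean-contaminated, contaminated surgeries".
- Pre/post comparison: "Chi-square test, independent sample t test or Mann-Whitney U test will be used for the statistical comparisons".

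The endpoint in section 3.7 is "The rate of surgical site infection till 30 days after surgery (90 days if implant) using CDC definition of SSI".

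The protocol expects deaths in this population. Section 3.11 (Sample Size and Power) allows for "15% loss to follow up or death before reaching the primary endpoint at 30-days", without splitting the two causes. Section 3.8 lists deaths prevented as a secondary endpoint. Appendix V admits patients up to ASA class V. No section gives a mortality figure, overall or by wound class, and none says how a death before SSI enters the curves.

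**The concern.** A patient who dies without an SSI can no longer acquire one. A Kaplan-Meier curve for a single event has no state for death, so the usual practice is to censor such patients at death. One minus the curve then estimates the infection risk in a setting where nobody dies first. That is higher than the proportion of operated patients who actually become infected, provided some SSIs occur after some of the deaths.

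The protocol names this estimator for the purpose of showing incidence, so this is a stated choice and not a detail left open. Two things are at stake. The plotted SSI incidence would be somewhat too high. If the package also reduced deaths, which the protocol hopes to show, the overstatement would be larger before the intervention than after it, and curves drawn by phase would flatter the absolute reduction.

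**Working it through.** **Inputs from section 3.11.** The anticipated SSI proportions, before and after, are 8% and 5% (clean), 12% and 8% (clean-contaminated), and 30% and 20% (contaminated). "The sample sizes were based on 90% power, a 5% two-sided significance level".

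**The plan's own figure.** The protocol gives no figure for the curves. Its sample sizes do show what the percentages mean. A two-proportion calculation (pooled variance, two-sided 5%, 90% power, no continuity correction) gives 1418, 1181 and 392 evaluable patients per phase. Multiplied by 1.15 these become 1631, 1359 and 451, against the stated 1630, 1350 and 450. Dividing by 0.85 gives 1669, 1390 and 462, within 3% of the stated figures. The percentages are therefore treated as proportions infected by the end of follow-up, which is the benchmark used here.

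**Assumption.** The share who die before SSI, F2, is not in the documents. It is varied from 1% to 15%. The last value would make the whole loss-or-death allowance deaths, which is an extreme.

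**Formula.** Let F1 be the true proportion infected. With constant cause-specific hazards for SSI and death over the follow-up window:

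- Aalen-Johansen returns F1.
- One minus Kaplan-Meier, with deaths censored, returns 1 − (1 − F1 − F2)^(F1/(F1 + F2)).

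Example, contaminated, F1 = 0.30 and F2 = 0.05: 1 − 0.65^(0.30/0.35) = 1 − 0.6913 = 30.87%, an excess of 0.87 points.

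**One minus Kaplan-Meier at baseline:**

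| F2 (assumed) | Clean, true 8% | Clean-contaminated, true 12% | Contaminated, true 30% |
| --- | --- | --- | --- |
| 1% | 8.04% | 12.06% | 30.17% |
| 2% | 8.08% | 12.13% | 30.34% |
| 5% | 8.21% | 12.32% | 30.87% |
| 10% | 8.44% | 12.67% | 31.83% |
| 15% | 8.69% | 13.05% | 32.87% |

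Over 2% to 5% death the excess runs from 0.08 to 0.87 points. If all deaths came before any SSI, the curve would reach F1/(1 − F2). At 5% death that is an excess of 0.42, 0.63 and 1.58 points in the three classes. If all deaths came after the last SSI, there would be no excess.

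**Pre/post difference read from the curves, contaminated class (true difference 10.0 points):**

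- 5% death in both phases: 30.87 − 20.56 = 10.3 points.
- 5% before, 2% after: 30.87 − 20.22 = 10.7 points.
- 10% before, 5% after: 31.83 − 20.56 = 11.3 points.

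**Which wound class is affected most.** With 5% death in every class the relative excess is nearly the same (2.7%, 2.7% and 2.9%), and the absolute excess is largest in the contaminated class. With assumed mortality of 1%, 2% and 5% from clean to contaminated, the excess is 0.04, 0.13 and 0.87 points. With a reversed gradient of 10%, 5% and 1% it is 0.44, 0.32 and 0.17 points, so the ranking turns over.

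**The case against.** The strongest reply is that the protocol never says deaths are censored, and that such handling is commonly left to a statistical analysis plan, which is not shown here. The first half is true: censoring is inferred from the ordinary use of the named method. But the protocol does fix the estimator and its purpose, and a single-event Kaplan-Meier curve cannot represent death as a separate outcome.

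A second reply is that the primary outcome is expressed per person-time, which is a cause-specific measure, and under constant hazards one minus Kaplan-Meier is its direct transform. That is fair as a statement about hazards, and it is why log-rank and Cox remain usable. It does not make the curve a display of the proportion infected, which is the quantity the trial is powered on.

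Third, the effect is small and descriptive. This stands.

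A reader might also infer more than the documents support:

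- *The contaminated class is distorted most.* This needs mortality by wound class, which is not given. Neurosurgery and ASA V patients are eligible and such operations can be clean, while dirty wounds are excluded, so the gradient is not obvious.
- *The primary result is biased.* The pre/post comparison is assigned to other tests, not to these curves.
- *Changing the plot alone makes it match the chi-square proportions.* Section 3.11 groups death with loss to follow-up, which may mean that patients who die leave the denominator. The reported proportion would then be F1/(1 − F2). In the contaminated class at 5% death that is 31.6%, against 30.9% from Kaplan-Meier and 30.0% from Aalen-Johansen. The denominator has to be settled as well.
- *Dates of death are already collected.* No readable section names this item. Person-time does require exit dates, so it is a reasonable expectation, not a documented fact.

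**Conclusion.** The point holds as a minor improvement to a named descriptive method. Used in the ordinary way, the planned curves overstate SSI incidence whenever deaths precede SSI and infections continue to occur afterwards. Under constant hazards the excess is about 0.1 to 0.9 points at 2% to 5% death before SSI, and up to 2.9 points in the extreme case where the full 15% allowance is death. A fall in deaths between phases would add somewhat to the apparent absolute reduction.

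These sizes rest on assumed mortality and on the anticipated SSI rates in section 3.11. Deaths concentrated early would enlarge them and late deaths would shrink them. Deaths after an SSI cause no such distortion. The sample sizes, the chi-square comparison, and the log-rank and Cox analyses read as cause-specific are not put in question.

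**What to change.** In section 3.9 and the synopsis:

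- Replace the Kaplan-Meier incidence plot with Aalen-Johansen cumulative incidence curves, by phase within each wound class, with death before SSI as a competing event. Read them at 30 days, and at 90 days for implant patients.
- Keep the log-rank test and the Cox model, labelled as cause-specific.
- State that patients who die without SSI stay in the denominator of the reported 30-day proportion as non-events. Curve and proportion then agree apart from loss to follow-up.

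The cost is a few sentences. Date of death must be an item in the case record form, and software other than SPSS 23 may be needed for this plot; section 3.9 already leaves the choice of plotting software open. The sample size and the primary test do not change.

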## Analysis of Qualitative data

## We will have qualitative data in two phases of our study. IDIs will be conducted in phase 1 (formative study) as the design of the same is a mixed-method, sequential exploratory design. IDIs will also be conducted with key stakeholders (surgeons, health care professionals and nursing officials involved) to evaluate their perception of the impact and feasibility of interventions at 6 months post-intervention phase and suggestions to improve the multipronged interventions (Phase 4). Thematic analysis will be the analytical framework used for the qualitative analysis.

All interviews will be transcribed in English. The PI and Co-PIs will read through the responses in the qualitative practice assessment, observation notes and interview transcripts, creating memos where necessary. All responses will be thematically coded to facilitate the identification and analysis of patterns or themes in the data set ^21,22^. Themes will be generated from the initial codes. Themes will be reviewed, named and documented. Multiple thematic codes will be shared with all members of the research team to guide the development of the multipronged interventions.

## Sample Size and Power

The three strata based on the type of the surgery (clean, clean-contaminated and contaminated) will be separately powered, based on different baseline SSI rates extracted from Indian study showing prevalence of SSIs in general surgery patients.^7,8^ The sample sizes were based on 90% power, a 5% two-sided significance level and 15% loss to follow up or death before reaching the primary endpoint at 30-days. For the clean surgeries, anticipating the baseline average SSI rate of 8%, a 3% absolute reduction in SSI to 5% will be taken as clinically significant and would require 3260 patients in total (1630 patients in pre-intervention and intervention each). For the clean-contaminated surgeries, anticipating the baseline average SSI rate of 12%, a 4% absolute reduction in SSI to 8% will be taken as clinically significant (i.e relative risk of 0.67) and would require 2700 patients in total (1350 in pre-intervention and intervention each). For the contaminated surgeries, anticipating higher baseline SSI rate of 30%, a 10% absolute reduction in SSI to 20% will be taken as clinically significant and would require 900 patients in total (450 in pre-intervention and intervention each).

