| **Number of Participants** | The three types of surgeries (clean, clean-contaminated and contaminated) will be separately powered, based on different baseline SSI rates. The sample sizes were based on 90% power, a 5% two-sided significance level and 15% loss to follow up or death before reaching the primary endpoint at 30-days. For the clean surgeries, anticipating the baseline average SSI rate of 8%, a 3% absolute reduction in SSI to 5% will be taken as clinically significant and would require 3260 patients in total. For the clean-contaminated surgeries, anticipating the baseline average SSI rate of 12%, a 4% absolute reduction in SSI to 8% will be taken as clinically significant and would require 2700 patients in total. For the contaminated surgeries, anticipating higher baseline SSI rate of 30%, a 10% absolute reduction in SSI to 20% will be taken as clinically significant and would require 900 patients in total. |
| **Study Duration** | Each subject’s participation will last for 30 days or 90 days if implant in situ. |
| **Study Phases** | The plan is to adopt a four- phased strategy, each addressing specific research question. Phase-I will involve formative research and practice analysis. Phase-II will involve co-development of the multipronged interventions. Phase-III will involve deployment of the multipronged interventions and process evaluation. Phase-IV will involve impact assessment and dissemination of results. |
| **Primary endpoint** | The rate of surgical site infection till 30 days after surgery (90 days if implant) using CDC definition of SSI in pre-intervention versus post-intervention phase for clean, clean-contaminated and contaminated surgeries |

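### The stated sample sizes give about 89% power, not 90%, once the protocol's own 15% loss is taken off (minor)

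*Protocol*

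**What the plan says.** Section 3.11 (Sample Size and Power) powers the three wound classes separately. It gives the design values as "The sample sizes were based on 90% power" and "a 5% two-sided significance level", and allows for "15% loss to follow up or death before reaching the primary endpoint at 30-days". The synopsis (Number of Participants) gives the same design values.

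The assumed rates and resulting sizes are:

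- Clean: "anticipating the baseline average SSI rate of 8%, a 3% absolute reduction in SSI to 5" percent; the study "would require 3260 patients in total (1630 patients in pre-intervention and intervention each").
- Clean-contaminated: "anticipating the baseline average SSI rate of 12%, a 4% absolute reduction in SSI to 8" percent; the study "would require 2700 patients in total (1350 in pre-intervention and intervention each").
- Contaminated: 30% falling to 20%; the study "would require 900 patients in total (450 in pre-intervention and intervention each").

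The synopsis repeats the three totals (3260, 2700 and 900) without the split by phase. Neither place gives the sample-size formula, the number before the loss allowance, or how the 15% was applied.

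**The concern.** If 15% of enrolled patients do not reach the endpoint, 85% remain, so the number to enrol is the evaluable number divided by 0.85. Multiplying by 1.15 instead gives too few, because 1.15 × 0.85 = 0.9775: about 2% of the evaluable patients needed are then missing. The stated sizes look like the product of that shortcut.

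What is at stake is the accuracy of a printed claim. The protocol makes the 90% statement for three separate strata, and all three can be checked from its own inputs. Section 5 plans publication of the protocol, so readers will be able to repeat the check.

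**Working it through.** **Inputs (Section 3.11).** Two-sided 5%, so z = 1.960; 90% power, so z = 1.2816; equal phases; rates p1 and p2 of 8% and 5%, 12% and 8%, 30% and 20%; loss 15%. Section 3.9 names the chi-square test and mentions no continuity correction. The variance formula is not stated, so both usual forms are shown.

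**Step 1. Evaluable patients per phase for 90% power.** Let d = p1 − p2, p̄ = (p1 + p2)/2, A = 2p̄(1 − p̄) and B = p1(1 − p1) + p2(1 − p2).

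- Pooled: n = (1.960√A + 1.2816√B)² / d²
- Unpooled: n = (1.960 + 1.2816)² × B / d² = 10.507 × B / d²

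Clean surgery, unpooled: B = 0.0736 + 0.0475 = 0.1211, so n = 10.507 × 0.1211 / 0.0009 = 1413.8.

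| Stratum | Pooled n | Unpooled n |
|---|---|---|
| Clean | 1417.0 | 1413.8 |
| Clean-contaminated | 1180.0 | 1176.8 |
| Contaminated | 391.9 | 388.8 |

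**Step 2. Reproduce the stated sizes.**

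| Stratum | Stated | Pooled × 1.15 | Unpooled × 1.15 | Pooled / 0.85 | Unpooled / 0.85 |
|---|---|---|---|---|---|
| Clean | 1630 | 1629.6 | 1625.9 | 1667.1 | 1663.3 |
| Clean-contaminated | 1350 | 1357.0 | 1353.4 | 1388.2 | 1384.5 |
| Contaminated | 450 | 450.7 | 447.1 | 461.1 | 457.4 |

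The unpooled formula times 1.15, rounded to the nearest ten, gives exactly 1630, 1350 and 450. The pooled formula times 1.15 comes within 1%, but its 1357 would round to 1360. Division by 0.85 gives none of the stated figures under either formula. Versions with a continuity correction, with 80% power, or with a one-sided 5% level do not reproduce them either.

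**Step 3. Power after the stated loss.** This step does not depend on how the 15% was applied. With m = 0.85 × stated N:

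- Pooled: power = Φ[(d − 1.960√(A/m)) / √(B/m)]
- Unpooled: power = Φ[d / √(B/m) − 1.960]

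Clean surgery, pooled: m = 1385.5, √(A/m) = 0.009366, √(B/m) = 0.009349, so (0.03 − 0.018358) / 0.009349 = 1.245 and power is 89.3%.

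| Stratum | Evaluable m | Power, pooled | Power, unpooled |
|---|---|---|---|
| Clean | 1385.5 | 89.3% | 89.4% |
| Clean-contaminated | 1147.5 | 89.2% | 89.3% |
| Contaminated | 382.5 | 89.3% | 89.5% |

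**Step 4. Loss at which 90% still holds.** This is 1 − n / stated N. Pooled: 1 − 1417.0/1630 = 13.1%, 1 − 1180.0/1350 = 12.6%, 1 − 391.9/450 = 12.9%. Unpooled: 13.3%, 12.8% and 13.6%.

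**Step 5. Sizes that would keep 90% at 15% loss.** One rounding route is used throughout: pooled n rounded up (1418, 1181, 392), divided by 0.85 and rounded up again. This gives 1669, 1390 and 462 per phase, or totals of 3338, 2780 and 924. The sum is 7042, against 3260 + 2700 + 900 = 6860: 182 more patients, or 2.7%.

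**The case against.** The best reply is that the difference is too small to matter. Power is short by 0.5 to 0.8 points, and the inputs are not known to that precision. If the clean post-intervention rate were 5.1% instead of 5.0%, power at 1385.5 per phase would be 87.0%, a larger change than the one at issue. For clean-contaminated surgery, Section 1.1 itself cites rates of about 10% and 15.5% against the 12% used. This stands, and it is why the point is minor. It does not make the printed 90% correct: the shortfall has the same sign in all three strata under both formulas.

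It can also be said that lost patients are not wholly lost. Section 3.9 expresses the primary rate per person-time and plots Kaplan-Meier curves, and Sections 3.5 and 4.1 provide for late follow-up, by telephone if necessary. That is fair, but Section 3.11 makes its allowance for patients lost before the endpoint, and the check follows that allowance.

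Third, Section 3.3.2 projects seven sites with about 1000 to 1500 patients each, so about 7000 to 10500. The recalculated 7042 is 1006 per site, which nearly all of that range covers. This also stands, although the projection is not split by stratum and so secures no single stratum.

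A reader might infer two stronger things. One is that the protocol says it multiplied by 1.15. It does not; that is an inference from the fit of the numbers, and the fit is closest with the unpooled formula. The other is that the study is materially underpowered or must enrol more. A gap below one point does not support that.

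**Conclusion.** Wrong as written, and minor. The stated sizes less the stated loss give about 89% power in each stratum (89.2% to 89.5%), and 90% holds only up to about 13% loss. This rests on the protocol's own rates, significance level and loss, a comparison of two proportions without continuity correction, and lost patients contributing nothing. The shortfall follows whatever inflation step was used; n × 1.15 is the likely explanation but is not documented. No design decision or later conclusion would change because of it.

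**What to change.** Keep the planned 3260, 2700 and 900, and restate power as about 89% per stratum after 15% loss or death. Alternatively, keep 90% and state the allowance as about 13%. Make the same change in Section 3.11 and in the synopsis, and add one sentence to Section 3.11 naming the formula and how the allowance was applied. The cost is a text edit in two places, with no extra patients.

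If the sponsor prefers to keep both 90% and 15%, the totals become 3338, 2780 and 924 by the rounding route shown above, which is 182 more patients overall.

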# STUDY ADMINISTRATION

## Data collection and management

Patients planned for general surgical procedures (elective or emergency) will be screened for inclusion in the study based on inclusion and exclusion criteria.

The data collection during baseline, post-intervention phase for the surgical patients undergoing elective or emergency surgery will be done by the Infection control nurse and research fellow in the standardized data collection form including but not limited to the data on timing of antimicrobial prophylaxis given, time of start of surgery, vitals, re-dosing of antimicrobial prophylaxis, time of stoppage of surgery, type of surgery (name of surgery; clean/clean-contaminated/contaminated/dirty), aseptic precautions taken or not, information on drains in situ, post-operative care, details of post-operative antimicrobials. The patient will be followed up regularly till discharge and data on SSI, antimicrobials, clinical outcome will be recorded. The patient will be called in-person for follow-up to ODP at 30-day to know the clinical status and outcome of the patient. Any unplanned visit to OPD or emergency will be noted with the reason of the visit.

If follow-up is not possible at 30 days after surgery, patients will be followed up as soon after this as possible or telephonically. If patient developed SSI before postoperative day 30, they will still be reviewed at 30 days after surgery to record secondary outcomes.

In intervention phase, in addition the checklist of multipronged interventions will be checked for implementation assurance along with the data collection form.

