## Study Duration, Enrollment and Number of Sites

### Duration of Study Participation

The study participation will last for 30-days or 90 days if implant placement during surgery. Each subject will be included in the study on pre-operative day-1 and followed till discharge. After discharge, the patient will be reviewed in the OPD or followed up telephonically till 30-days of the surgery or 90 days if implant placed (where the day of surgery will be taken as POD-0) for any evidence of surgical site infection. Any re-admission in-between the discharge and 30-days will be noted along with the reason of re-admission.

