## Subject Completion/Withdrawal

The patients who take leave from hospital against medical advice (LAMA) will be contacted for follow-up at 30-days for the outcome.

If follow-up is not possible at 30 days after surgery, patients will be followed up as soon after this as possible.

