# Appendix-II: who SURGICAL SITE INFECTION SURVEILLANCE POST-OPERATIVE DATA COLLECTION FORM

# Appendix-IiI: DIAGNOSIS OF SURGICAL SITE INFECTION AS PER CDC

| **Superficial incisional SSI :** Must meet the following criteria:  Date of event occurs within 30 days following the operative procedure (where day 1 = the procedure date) **AND** involves only skin and subcutaneous tissue of the incision  **AND**  patient has at least ***one*** of the following:   1. purulent drainage from the superficial incision. 2. organism(s) identified from an aseptically-obtained specimen from the superficial incision or subcutaneous tissue by a culture or non- culture based microbiologic testing method which is performed for purposes of clinical diagnosis or treatment (for example, not Active Surveillance Culture/Testing [ASC/AST]). 3. a superficial incision that is deliberately opened by a surgeon, physician* or physician designee and culture or non-culture based testing of the superficial incision or subcutaneous tissue is not performed **AND** patient has at least one of the following signs or symptoms: localized pain or tenderness; localized swelling; erythema; or heat. 4. diagnosis of a superficial incisional SSI by a physician. |
| --- |
| **Deep incisional SSI**  Must meet the following criteria:  Date of event occurs within 30 or 90 days following the operative procedure (where day 1 = the procedure date) **AND** involves deep soft tissues of the incision (for example, fascial and muscle layers) **AND** patient has at least ***one*** of the following:   1. purulent drainage from the deep incision. 2. a deep incision that is deliberately opened or aspirated by a surgeon, physician or spontaneously dehisces   **AND**  organism(s) identified from the deep soft tissues of the incision by a culture or non-culture based microbiologic testing method which is performed for purposes of clinical diagnosis or treatment (for example, not Active Surveillance Culture/Testing [ASC/AST]) or culture or non- culture based microbiologic testing method is not performed. A culture or non-culture based test from the deep soft tissues of the incision that has a negative finding does not meet this criterion.  **AND**  patient has at least ***one*** of the following signs or symptoms: fever (>38°C); localized pain or tenderness.   1. an abscess or other evidence of infection involving the deep incision detected on gross anatomical exam, histopathologic exam, or imaging test. |

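### Follow-up instructions for implant patients conflict: the primary endpoint runs to day 90, but the data-collection, withdrawal and sample-size sections stop at day 30

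*Protocol*

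**What the plan says.** **Places that give implant patients 90 days**
- Section 3.7 (Primary Endpoint): "The rate of surgical site infection till 30 days after surgery (90 days if implant) using CDC definition of SSI". The synopsis and section 3.9 use the same window.
- Section 3.3.1, which is itself a follow-up procedure: after discharge the patient is "reviewed in the OPD or followed up telephonically till 30-days of the surgery or 90 days if implant placed".
- The staff justification in the budget, which funds a nurse for 30-day follow-up, or 90-day follow-up with an implant.

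**Places that name day 30 with no implant exception**
- Section 4.1, the instruction to the staff who collect the data: "The patient will be called in-person for follow-up to ODP at 30-day to know the clinical status and outcome of the patient". Its missed-visit rule is "If follow-up is not possible at 30 days after surgery, patients will be followed up as soon after this as possible or telephonically". Its review of patients who have already had an infection is also set at day 30.
- Section 3.5: patients who leave against medical advice "will be contacted for follow-up at 30-days for the outcome". The missed-visit rule there also starts from day 30.
- Section 3.11: the 15% allowance for loss or death is described as occurring before a primary endpoint at 30 days.

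**Definition of the event**
- Appendix-III, superficial infection: "Date of event occurs within 30 days following the operative procedure (where day 1 = the procedure date").
- Appendix-III, deep infection: "Date of event occurs within 30 or 90 days following the operative procedure (where day 1 = the procedure date"). The appendix does not say what decides between 30 and 90.
- Section 3.3.1 counts the day of surgery as day 0; Appendix-III counts it as day 1.

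**The concern.** Section 4.1 is the text that the infection control nurse and research fellow will work from. It describes one outcome visit after discharge and gives no later contact for patients with an implant. If a site takes that as its schedule, infections arising on days 31-90 are recorded only if the patient happens to return.

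The design makes this matter more than it would in a randomised trial. The comparison is pre against post at seven sites with no concurrent control, so a change in how completely late infections are found between the two phases cannot be told apart from an intervention effect. The strata most exposed are those that contain implant procedures; orthopaedics and neurosurgery are among the eligible specialties.

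There is also a smaller question of what counts. Read on its own, the parenthesis in 3.7 covers any surgical site infection to day 90 in an implant patient. Appendix-III would exclude a superficial infection on day 45 in the same patient.

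**Working it through.** **1. The plan's own figure (clean surgery)**

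Inputs from section 3.11: 8% against 5%, two-sided 5% level, 90% power, equal phases, 15% loss, 1630 per phase.

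Formula (pooled variance, no continuity correction):

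n = [1.960·√(2·p̄(1−p̄)) + 1.282·√(p₁(1−p₁) + p₂(1−p₂))]² / (p₁−p₂)², with p̄ = 0.065.

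This gives 1418 per phase. Multiplying by 1.15 gives 1631; dividing by 0.85 gives 1669. The stated 1630 is reproduced. With 15% lost from 1630, power is 89.3%. The sample size is not in question here; only its 30-day wording is.

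**2. The instructions side by side**

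| Place | Outcome contact, no implant | Outcome contact, implant |
|---|---|---|
| 3.3.1 | clinic or telephone to day 30 | clinic or telephone to day 90 |
| 3.7, 3.9, staff justification | 30 days | 90 days |
| 4.1 visit and missed-visit rule | day 30 | none stated beyond day 30 |
| 3.5 left against advice, missed visit | day 30 | none stated beyond day 30 |
| 3.11 | 30 days | no separate time given |

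For patients without an implant all rows agree. For implant patients the first two rows cannot be carried out from the instructions in the next two.

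**3. How much could be missed (illustration only)**

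The documents give neither the share of clean cases with an implant (f) nor the share of those patients' infections that arise on days 31-90 (s). Assumed: f = 20-40%, s = 10-30%, the stated 8% is a full-window rate, and implant patients have the same infection rate as the rest.

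Missed = f × s × 8%.
- Low: 0.20 × 0.10 × 8% = 0.16 points.
- High: 0.40 × 0.30 × 8% = 0.96 points.

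**4. Same loss in both phases**

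Both rates shrink by the factor 1 − f·s, and the relative effect is unchanged. Power is for 1630 per phase with 15% lost.

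| f, s | Captured rates | Power |
|---|---|---|
| 10%, 10% | 7.92% vs 4.95% | 89.0% |
| 20%, 10% | 7.84% vs 4.90% | 88.7% |
| 30%, 30% | 7.28% vs 4.55% | 86.2% |
| 40%, 30% | 7.04% vs 4.40% | 84.9% |
| 50%, 50% | 6.00% vs 3.75% | 78.6% |

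**5. Loss in one phase only (worst case)**

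On proportions, the whole missed amount enters the difference: 0.16/3 = 5% to 0.96/3 = 32% of the 3-point target.

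Section 3.9 also expresses the rate per person-time, where days are lost along with events. Suppose baseline stops at day 30, the post phase runs to day 90, and there is no true effect. Ignoring time lost after an event, mean follow-up in the post phase is 0.2·90 + 0.8·30 = 42 days, or 0.4·90 + 0.6·30 = 54 days.
- Low: 7.84%/30 = 2.61 against 8%/42 = 1.90 per 1000 person-days, a fall of 27%.
- High: 7.04%/30 = 2.35 against 8%/54 = 1.48 per 1000 person-days, a fall of 37%.

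The same mismatch would raise the post-phase proportion, so even the direction of the bias depends on the measure.

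**The case against.** **The 90-day endpoint is provided for.** A reader might infer from 4.1 that the endpoint is simply not collected. The protocol as a whole does not support that. Section 3.3.1 has implant patients "followed up telephonically till 30-days of the surgery or 90 days if implant placed", and the budget staffs for it. Sections 4.1 and 3.5 do not say that day 30 is the last contact. This stands: the defect is that the instructions conflict, not that day-90 follow-up is absent. It does not remove the point, because 4.1 and 3.5 are operating rules and neither carries the exception.

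**Appendix-III does not contradict the endpoint.** A reader might also infer a contradiction over superficial infections. Section 3.7 sets its window together with the CDC definition, and both the introduction and Appendix-III give that definition as superficial to 30 days and deep to 30 or 90. The natural reading excludes a superficial infection on day 45. This largely stands. What remains is an ambiguity: 3.7 does not name the depths that count after day 30, and the appendix does not tie its 90 days to implants.

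**Section 3.11 instructs no site.** True. It describes an attrition assumption and adds nothing about collection, but its endpoint timing is wrong for implant patients.

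**No differential loss is stated.** The same text governs both phases, and Phase-IV calls for the same parameters on the same form as baseline. This stands, so the 5-32% figure is not an estimate of bias. It needs complete loss at every site in one phase and complete capture in the other. One route to unequal ascertainment does exist: the per-patient checklist is used only in the intervention phase, and its template has an item on surveillance by the CDC definition. That template is only an example and says nothing about day 90.

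**The day-count shift is trivial.** It affects boundary-day events only and is the same in both phases. It is worth tidying and no more.

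**Conclusion.** The point holds as a conflict between stated rules on the primary endpoint. Sections 3.3.1, 3.7, 3.9 and the staff justification run to 90 days for implant patients; 4.1 and 3.5 give day-30 contact with no exception, and 3.11 times the endpoint at 30 days. Sites that follow 4.1 or 3.5 as written could miss implant infections on days 31-90.

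The consequence cannot be sized from the documents. Under the assumed shares (20-40% implants, 10-30% late), 0.16-0.96 points of the 8% clean rate would be missed. If the loss is equal in both phases, power falls from 89.3% to between 88.7% and 84.9%, with no bias in the relative effect. If it is unequal, the comparison is biased by an amount and in a direction that depend on the pattern of loss and on whether proportions or person-time rates are compared. The one-phase figures are outer limits, not expectations.

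The documents do not support saying that the endpoint goes uncollected, or that Appendix-III overturns it. The change should be made, since the primary endpoint is affected and the remedy is simple.

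**What to change.** - **4.1 and 3.5:** carry over the 90-day implant follow-up from 3.3.1 (clinic or telephone), including for patients who leave against medical advice, and give the missed-visit rules a day-90 counterpart.
- **3.11:** replace the 30-day wording with the endpoint's window (30 days, or 90 with an implant), and confirm that the 15% allowance is meant to cover the longer follow-up.
- **3.7 and Appendix-III:** state which infection depths count after day 30, consistently with the appendix, and link the appendix's 90-day deep window to implants.
- **Day-count:** use one convention for the day of surgery throughout.
- **Case record form:** record implant status and the date of event, count by that date, and apply the same window in the pre- and post-intervention phases.

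The cost is protocol wording and, if not already on the form, the fields named above. The 90-day follow-up is already in 3.3.1 and in the staff justification, so no new procedure is added.
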